## Abstract

**Introduction:**

Chronic musculoskeletal pain is a complex medical condition that can significantly impact quality of life. Patients with chronic pain demonstrate attentional biases towards pain-related information. The therapeutic benefits of modifying attentional biases by implicitly training attention away from pain-related information towards neutral information have been supported in a small number of published studies. Limited research however has explored the efficacy of modifying pain-related biases via the internet. This protocol describes a randomised, double-blind, internet-delivered attentional bias modification intervention, aimed to evaluate the efficacy of the intervention on reducing pain interference. Secondary outcomes are pain intensity, state and trait anxiety, depression, pain-related fear, and sleep impairment. This study will also explore the effects of training intensity on these outcomes, along with participants’ perceptions about the therapy.

**Methods and analysis:**

The study is a double-blind, randomised controlled trial with four arms exploring the efficacy of online attentional bias modification training versus placebo training theorised to offer no specific therapeutic benefit. Participants with chronic musculoskeletal pain will be randomised to one of four groups: (1) 10-session attentional modification group; (2) 10-session placebo training group; (3) 18-session attentional modification group; or (4) 18-session placebo training group. In the attentional modification groups, the probe-classification version of the visual-probe task will be used to implicitly train attention away from threatening information towards neutral information. Following the intervention, participants will complete a short interview exploring their perceptions about the online training. In addition, a subgroup analysis for participants aged 16–24 and 25–60 will be undertaken.

**Ethics and dissemination:**

This study has been approved by the University of Southampton Research Ethics Committee. Results will be published in peer-reviewed journals, academic conferences, and in lay reports for pain charities and patient support groups.

**Trial registration number:**

NCT02232100; Pre-results.

Strengths and limitations of this studyThis protocol describes an internet-delivered intervention to explore the efficacy of attentional bias modification training in patients with chronic musculoskeletal pain.The study will recruit a diverse sample of participants in terms of age, socioeconomic status and geographical region.Results will provide important information regarding dose effects, age effects, and participants’ experiences and attitudes using the online intervention.There is limited control over the conditions under which training is completed.Independently verifying participant diagnosis is impossible.

## Introduction

Chronic musculoskeletal pain (CMSK) is pain arising from the bones, muscles, ligaments, tendons and/or joints lasting for more than 3 months.^1^ Prevalence estimates of CMSK vary considerably, affecting between 11.4% and 24% of the adult population^2^ and between 4% and 40% of children and adolescents.^3^ Negative effects on quality of life are commonly reported in adult^4–7^ and paediatric^8–11^ CMSK populations, and theory-driven research^12–14^ has shown that patients with chronic pain exhibit attentional biases (ie, a selective attention) for salient pain-related words (eg, refs 15–18) and images (eg, refs 19 20) relative to neutral information. Three meta-analyses have supported the presence of attentional biases in patients with chronic pain,^21–23^ although evidence for the time course of such biases is mixed. Specifically, two meta-analyses reported larger effect sizes when stimuli are presented for longer than 1000 ms,^21 23^ whereas a recent analysis found evidence of bias for presentation times of 500–1000 ms but not when stimuli are presented for longer than 1000 ms.^22^ Despite this inconsistency, attentional biases are commonly shown in chronic pain, and preliminary research has explored the effects redirecting attention may have on pain and pain-related distress using attentional bias modification (ABM) techniques. ABM is a computer-based intervention which implicitly trains attention away from threat-related cues towards neutral information, and is frequently achieved through a modified version of the visual-probe task^24^ (figure 1).

**Figure 1 F1:**
[figure not shown]
A graphical representation of a typical visual-probe task training trial with linguistic stimuli.

Two small randomised controlled trials (RCTs)^25 26^ and one pilot study^27^ have used the modified probe-classification version of the visual-probe task to assess ABM in adults with chronic pain. Carleton and colleagues^25^ found participants receiving ABM showed significant reductions from pre-ABM to post-ABM in anxiety sensitivity and fear of pain, and marginally significant reduction in current pain severity. No significant reductions were found in illness/injury sensitivity or pain anxiety. Significantly more patients receiving ABM reported clinically significant change in current pain compared with those in the placebo group (44% vs 17%, respectively). Attentional bias scores were not recorded, and therefore the researchers could not comment on mechanisms of action. Sharpe and colleagues^26^ found participants receiving ABM, compared with those in a placebo group, showed significant improvements in pain-related disability after the ABM. No significant improvements were found for pain, fear of pain, fear of reinjury, depression, anxiety, stress, anxiety sensitivity or pain self-efficacy. At 6-month follow-up (and after all participants had undergone eight sessions of cognitive behavioural therapy (CBT)) the ABM group, compared with the placebo group, showed significant improvements in disability and anxiety sensitivity, and marginally significant improvements in fear of reinjury. No other significant effects were found, and the mechanism of action could not be established as ABM was not found to change patterns of attentional bias across time. Schoth and colleagues^27^ reported statistically and clinically significant change from pre-ABM to post-ABM in pain intensity, pain interference, anxiety and depression. Assessed via the McGill Pain Questionnaire,^28^ significant changes from pre-ABM to post-ABM were shown for total pain, affective pain and miscellaneous pain, but not sensory pain or evaluative pain. There was also no evidence that attentional biases changed across time.

One small RCT in adolescents with chronic pain randomised participants to either ABM, placebo training or waiting-list groups. No significant differences were found between the three groups in terms of pain, disability, pain catastrophising, anxiety, depression or objective measures of physical functioning (sit-to-stand task and cardio wall tasks), and no evidence was found that ABM changed attentional bias or attentional control compared with placebo and waiting-list conditions.^29^ Overall, while some studies have provided support for the benefits of ABM in adults, the evidence in regard to specific outcome variables is mixed and the mechanisms of action have yet to be established. Given the methodological shortcomings and small sample sizes of previous studies however, further research is needed to determine the therapeutic benefits of ABM for patients with chronic pain, along with the optimal form ABM should take and the impact of age on outcomes and intervention engagement. Considering the optimal form of ABM, a review of the broader cognitive bias modification (CBM) literature identified 12 published meta-analyses, 11 examining ABM specifically.^30^ Three out of six analyses found the number of sessions to be a significant moderator of CBM, and three out of nine analyses found the number of sessions to be a significant moderator of symptom outcomes. Although evidence is therefore mixed, it is nevertheless worth exploring whether the number of sessions impacts the patterns of attentional bias and pain-related outcomes in individuals with chronic pain.

This article presents a study protocol for a randomised, double-blind, internet-delivered ABM intervention. The results of a pilot think-aloud study informing the design of the intervention are also presented. The aim of this RCT is to assess the efficacy of internet-delivered ABM in improving pain and pain-related distress in people aged 16–60 with CMSK, and will report a subgroup by treatment effects using the two age brackets of 16–24 and 25–60. While only limited evidence has been found for age as a moderator of CBM on bias change and symptoms,^30^ it has been argued that the age of adolescence should be extended from 19 to 24 as the latter corresponds more closely to adolescent growth and popular understandings of this life phase.^31^ Furthermore, although use of the internet has been growing among all age groups, there are nevertheless still some differences in internet use and activity according to age (eg, in the UK, 1% of those aged 16–24 do not use the internet, compared with 7% of those aged 45–54),^32^ thus warranting a separate consideration of adolescent and adult participants. Overall, a diverse sample in terms of age, socioeconomic status and geographical region will be recruited, thus increasing generalisability of results to the CMSK population. The primary outcome measure is pain interference. Secondary outcome measures are pain intensity, state and trait anxiety, depression, pain-related fear and sleep impairment, and engagement to and satisfaction with the online visual-probe training task. Dose effects will be explored via the inclusion of 10-session vs 18-session conditions. It is hypothesised that participants in the intervention group, relative to those in the placebo group, will report significant reductions in pain interference, pain intensity, anxiety, depression, sleep impairment and pain-related fear at study endline. It is also hypothesised that dose will significantly moderate these findings, with greater effects in 18 compared with 10 sessions.

## Methods and analysis

### Participants

Participants will be recruited via press announcements, social media and patient organisations throughout the UK. Inclusion criteria will be (1) aged between 16 and 60 years old; (2) experiencing any type of CMSK (ie, any condition that involves pain lasting for more than 3 months and arises from the bones, muscles and/or joints); (3) able to sit at a personal computer for 40 min; (4) normal or corrected to normal vision; (5) access to the internet at least twice a week; (6) access to, and familiarity using, a Windows-based computer; (7) successful completion of primary school; and (8) living in the UK. Exclusion criteria will be (1) experiencing malignant CMSK (ie, pain due to a tumour); (2) a diagnosis of other forms of comorbid chronic pain (eg, chronic headache); and (3) a diagnosis of any psychiatric disorder, either currently or within the last 5 years. There are no restrictions placed on concomitant care, and participants are not required to make any changes to current treatments they may be receiving.

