### Randomisation and sample size

Block randomisation of size four, performed via a randomisation command in the LifeGuide platform,^36^ will be used to sequentially randomise eligible consecutive consenting participants to one of four groups: (1) 10-session attentional modification group (10AMG); (2) 10-session placebo training group (10PTG); (3) 18-session attentional modification group (18AMG); or (4) 18-session placebo training group (18PTG). This blocked randomisation will be performed separately for those aged 16–24 and those aged 25–60. An allocation concealment mechanism will be used to ensure neither participants nor researchers know the study group to which the next participant will be assigned. This will be automatically performed within the LifeGuide platform (see The intervention section), with participants provided access to appropriate AMG or PTG sessions. Participants randomised to either 10-session condition will receive ten 35 min online sessions across a 4-week period, while those randomised to either 18-session condition will receive eighteen 35 min online sessions across an 8-week period. All online sessions will be administered twice a week on a separate set of days (Monday–Thursday, Tuesday–Friday). Participants randomised to either AMG condition will receive attentional training via the modified training version of the probe-classification visual-probe task, while those randomised to either PTG condition will receive placebo training via the standard version of the probe-classification visual-probe task. To maintain the overall quality and legitimacy of the intervention, code breaks (ie, unblinding) will only occur in exceptional circumstances. Adherence will be monitored electronically via LifeGuide.

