### Procedure

Interested individuals will contact the researchers on the details provided in study advertisements and will be assessed against the inclusion and exclusion criteria via telephone interview. If eligible, they will receive a copy of the participant information sheet detailing the requirements and procedure of the study, along with a link to the study website which provides further details on ABM and the research team. If the individual consents to take part, they will be required to create an online ABM account. During registration, participants will select their preferred days for training, which will be either (1) Monday/Thursday or (2) Tuesday/Friday.

Session 1 is the baseline session, and includes the first assessment visual-probe task measuring attentional biases prior to beginning the intervention, along with the questionnaire battery assessing the primary and secondary outcome measures. Randomisation will take place following session 1, where participants will be informed of the length of their training (ie, 4 or 8 weeks). Participants randomised to either of the 10-session conditions will complete four pictorial and four linguistic training sessions, while those randomised to either of the 18-session conditions will complete eight pictorial and eight linguistic training sessions (baseline and endline assessment sessions comprise the remainder of the 10/18 sessions). Participants’ attentional biases will be reassessed at endline (ie, during the final session 10/18) using the same assessment version of the visual-probe task (ie, featuring the same stimuli) used at baseline and the same questionnaire battery. Participants randomised to either of the 18-session conditions will also have their attentional biases reassessed in session 10 after their training session.

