### The intervention

The intervention will be hosted using LifeGuide and iSurvey platforms, both developed by the University of Southampton. LifeGuide is an open-source software which allows researchers to create online interventions.^36^ iSurvey is a survey generation tool which allows researchers to create and disseminate questionnaires online. Participants will register for the intervention using LifeGuide, which will also host the majority of the questionnaires. iSurvey will be used to host the visual-probe tasks, along with the Engagement with the Online Training questionnaire and the Brief Pain Inventory,^37^ which appear at the end of every visual-probe task session. The flow of sessions is provided in figure 2, and examples of web pages are shown in figure 3. On loading the intervention home page, the individual is provided with a brief welcome to the website and rationale for the intervention. A recent review of cognitive bias meta-analyses concluded that effect sizes were smaller when biases were modified remotely compared with laboratory-based training.^30^ We therefore decided to provide information on the rationale behind ABMT in order to increase motivation and reduce attrition as much as possible, which also mirrors clinical practice that involves educating patients into chronic pain and the psychological interventions used in its management. Individuals are able to either create an iABMT account or log into their existing account. Before any session participants are asked to indicate whether they have enough time and are ready to begin the session. Participants are only permitted to complete one session per day. Should a participant complete their missed session on a subsequently scheduled date (eg, completing their scheduled session from Monday on Thursday instead), all remaining sessions are shifted back accordingly. This process retains the structure of the intervention.

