### Visual-probe tasks

The flow of visual-probe sessions is illustrated in figure 2. In total there will be eight linguistic and eight pictorial probe-classification visual-probe training tasks used in the study, each with different stimuli. A complete description of the stimuli including ratings of valence, arousal, pain intensity, written frequency and low-level features is provided in online supplementary material 1. To briefly summarise, each linguistic visual-probe task includes 32 threatening/neutral and 16 neutral/neutral word pairs. Each task includes eight threatening words from each of the following categories: sensory pain, affective pain, health threat and general threat. Each pictorial task includes 32 threatening/neutral and 16 neutral/neutral image pairs. Each task includes eight threatening images from the following categories: musculoskeletal pain, facial expressions of pain, health threat and general threat. A total of 384 trials are included in each task, with each stimuli pair presented four times for 500 ms and four times for 1250 ms. Within each exposure duration, each stimulus appears twice in the upper location of the screen and twice in the lower location.

10.1136/bmjopen-2019-030607.supp1Supplementary data

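### At session 10, the primary time point, the 18-session arms are assessed straight after a ninth training task, while the 10-session arms are assessed 3–4 days after their eighth

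*Protocol article*

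**What the plan says.** All references are to the protocol article.

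- **Participants:** one entry criterion is being "able to sit at a personal computer for 40 min".
- **Randomisation and sample size:** the shorter arms "will receive ten 35 min online sessions across a 4-week period" and the longer arms "will receive eighteen 35 min online sessions across an 8-week period". No session is given a different length. Training runs on Monday/Thursday or Tuesday/Friday. The trial is powered on pain interference at baseline and after session 10, attentional modification against placebo, pooled over the two session numbers.
- **Procedure:** session 1 is the baseline assessment. The 10-session arms then have four pictorial and four linguistic training sessions, the 18-session arms eight of each, and "baseline and endline assessment sessions comprise the remainder of the 10/18 sessions". For the longer arms it adds: "Participants randomised to either of the 18-session conditions will also have their attentional biases reassessed in session 10 after their training session".
- **Table 1, note on the evaluation phase:** this phase comprises the assessment visual-probe task and the questionnaires, and the 18-session arms also complete it during session 10. The Outcome measures section confirms that they receive the questionnaires after 10 sessions.
- **The intervention:** only one session a day is allowed. The engagement questionnaire and the Brief Pain Inventory, which yields the primary outcome, are described as instruments "which appear at the end of every visual-probe task session".
- **Visual-probe tasks:** for the training tasks, "A total of 384 trials are included in each task".
- **Quantitative analyses:** the primary analysis crosses stage, treatment and number of sessions. Further items compare treatments within each session number after 10 sessions, examine change from session 10 to endline in the 18-session arms, and compare all four arms at each time point.

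**The concern.** Pooling the two session numbers at session 10 makes sense if all arms have had the same exposure by then and are measured in the same way. The text sets up something different. In half the sample the reading comes in the same session as a training task. In the other half it comes at a session without training, some days after the last one. The training count also differs by one task.

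What is at stake is interpretation. A difference between 10- and 18-session arms at session 10 could reflect recency of training, one extra task or a longer session. It need not reflect anything about the longer programme. The within-group change from session 10 to endline in the 18-session arms has the same weakness, because it sets a reading taken just after training against one from an assessment-only session.

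There is also an internal inconsistency. A session that holds training, an assessment task and questionnaires is given the same 35 min as a session with training alone, and entry screens for only 40 min at a computer. A long session placed just before the primary outcome may also lose some participants before they record it.

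**Working it through.** **1. Session counts reproduce.** 1 baseline + 4 pictorial + 4 linguistic + 1 endline = 10. 1 baseline + 8 + 8 + 1 endline = 18.

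**2. Training received before the session-10 assessment.**
- 10-session arms: training in sessions 2–9, so 8 tasks. Session 10 is assessment only.
- 18-session arms: training in sessions 2–10, with session 10's training before its assessment, so 9 tasks.

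This takes one training task per training session.

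**3. Time since the last training task.**
- 10-session arms: one scheduled interval. Monday to Thursday or Tuesday to Friday is 3 days; Thursday to Monday or Friday to Tuesday is 4 days.
- 18-session arms: the same session.

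The text does not say whether the Brief Pain Inventory follows the training task or the assessment task when both fall in one session. Either way it is answered after training in that session.

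**4. Trial count reproduces.** (32 + 16) pairs × 8 presentations = 384.

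**5. Length of session 10 in the 18-session arms.** The stated 35 min cannot be rebuilt, because response time, inter-trial interval and questionnaire time are not given. The assessment task's trial count is not given either; 384 is assumed from the training tasks. Half the trials show stimuli for 500 ms and half for 1250 ms, after a 500 ms fixation:

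384 × 0.5 s + 192 × 0.5 s + 192 × 1.25 s = 192 + 96 + 240 = 528 s = 8.8 min of display time per task.

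With assumed responses of 0.4–1.0 s and intervals of 0–1 s, a task takes 11.4–21.6 min.

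| What is added to a 35 min training session | Total (min) | Ratio to 35 min |
|---|---|---|
| Display time of one assessment task | 35 + 8.8 = 43.8 | 1.25 |
| Assessment task with assumed responses and intervals | 35 + 11.4 to 35 + 21.6 = 46.4–56.6 | 1.33–1.62 |
| A whole assessment session at the stated 35 min | 35 + 35 = 70 | 2.0 |

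Every row exceeds both 35 and 40 min, and the first two contain no time for the added questionnaires.

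**6. Building from the parts instead.** Two tasks plus an assumed 10–15 min of questionnaires give 2 × 11.4 + 10 = 32.8 min to 2 × 21.6 + 15 = 58.2 min. The low end is below 40 min. At those task times, however, a session with one training task would fall well short of the stated 35 min.

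**7. Who is affected.** Two of four equal arms, so about 50 of the planned minimum of 100 participants.

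**8. Which analyses are touched.**

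| Analysis | Effect |
|---|---|
| Attentional modification vs placebo, pooled, after session 10 | Same on both sides; no bias from this alone, but an average over two timings |
| The same contrast within 10-session or within 18-session arms | Sound within each; not comparable with one another |
| Sessions factor and treatment-by-sessions term at session 10 | Confounded with recency, one extra task and session length |
| Four arms compared after session 10 | Confounded wherever a 10-session arm meets an 18-session arm |
| Within-group change, session 10 to endline, 18-session arms | Post-training reading against an assessment-only reading |
| Between-group part of that change (18-session arms) | Same on both sides |
| Baseline, endline and follow-up analysis | Not touched; endline is assessment only in all arms |

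**The case against.** The strongest reply is that the powered comparison is safe. Within each session number, attentional modification and placebo have an identical session 10. Allocation is equal, and number of sessions is a factor in the model. This stands: a reader might infer that the primary treatment contrast is biased, and the document does not support that. The plan also reports the contrast separately within the 10- and 18-session arms, so each timing can be seen on its own. The dose hypothesis is framed at endline, where all arms have an assessment-only session. Both points stand, and they limit the concern to the analyses marked in the second table above.

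A reader might also take the session to be about twice as long as in the 10-session arms, or say that it cannot possibly fit 40 min. Neither is established. Twice, or 70 min, is the upper end and counts the overhead of a whole session a second time. A build from the parts can come in under 40 min, though only by contradicting the stated 35 min.

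It is tempting to add that long sitting inflates the primary outcome. The document gives no figure for that. The score averages seven items, among them walking, work and sleep, which are not momentary readings; current pain intensity, a secondary outcome, is the more plausible target. The 40 min criterion is an entry minimum, not a measured limit for each participant.

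Finally, the flow figure is not available and an article condenses. That does not remove the point, because the order of training then assessment is stated outright, and no passage gives this session a longer duration, a break or a separate day.

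**Conclusion.** The point holds in a limited form, and the plan should be changed. At the primary time point half the sample is measured after 9 training tasks, the last in the same session. The other half is measured after 8, the last 3–4 days earlier. This follows from the stated session structure and does not depend on any timing assumption.

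The pooled contrast of attentional modification with placebo is not biased by this alone, but it estimates an average of two timings. The 10- versus 18-session terms and the four-arm comparison at session 10 are confounded, as is the within-group change from session 10 to endline in the 18-session arms.

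On duration, the combined session is inconsistent with the flat 35 min. Built on that figure it comes to about 44–70 min against a 40 min screen. That range assumes 384 trials in the assessment task and leaves questionnaire time unknown. How far the longer session would shift interference scores or raise dropout cannot be sized from the document.

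**What to change.** In the Procedure section and the note to Table 1, have the 18-session arms complete the session-10 assessment task and questionnaires before that session's training task. The order of task and questionnaires should be the same as in session 10 of the 10-session arms. All arms are then assessed after 8 training tasks, with the last one a scheduled interval earlier. The number and content of the training tasks do not change.

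An assessment-only log-on is preferable. Reordering within one session equalises training count and recency but leaves that session long; a separate log-on also matches its length. Because the platform allows one session a day, the text would need to say how this log-on fits the calendar.

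Then reconcile the 35 min statement (Randomisation and sample size) and the 40 min criterion (Participants) with the longest session that remains.

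The cost is a platform edit and, if a separate log-on is used, one extra log-on in two arms, which a few participants may miss.
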